## 12. STATISTICAL ANALYSIS

### 12.1. GENERAL CONSIDERATIONS

The primary endpoint in this trial is time to all-cause mortality through 60 days post-randomization. The primary analysis is the assessment of difference between the experimental treatment (CRRT+SCD) and the control treatment (CRRT alone) on the primary endpoint, and the assessment of this difference will be carried out at an overall two-sided 0.05 level of significance. Statistical treatment comparisons on secondary endpoints will also be carried out at an overall two-sided 0.05 level of significance, unless otherwise specified. Statistical analyses will be carried out using SAS version 9.1 or higher, and other appropriate

statistical software if necessary.

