## **12.6. SECONDARY ENDPOINTS**

- Renal Replacement Therapy dependency at day 60
- Time-to-Mortality through day 28
- Number of ventilator free days (VFD) at day 28
- Time-to-Mortality through day 60 for the Severe Septic patient(s)

Definitions for secondary endpoints are provided in Appendix D

For renal replacement therapy dependency, treatments will be compared on the number and percentage of patients with the incidence of the event using the Z test for proportions or the continuity-corrected z-test for proportions, depending on event rate. For time-to-mortality through day 28 and for time to mortality through day 60 for the severely septic patient sub-population, treatments will be compared using the log-rank test. For number of VFD at day 28, the sample size, mean, standard deviation, median, quartiles, and minimum and maximum will be presented for each treatment group. Treatment groups will be compared using the two-sample t-test. Health Economic endpoints are still under development will be discussed in a separate plan. These endpoints are not intended to support a PMA application.

In order to control the overall two-sided level of significance at 0.05 across the secondary endpoints, the Benjamini-Hochberg procedure will be used. For time-to-mortality analysis, patients who did not die will be censored at the time of analysis (day 28 or day 60) or at the time of premature withdrawal, whichever is earlier. Otherwise, given the secondary nature of these endpoints, no imputation for missing data will be performed; i.e., patients prematurely withdrawing prior to the time point at which the endpoint is measured will be excluded from the

analysis on that endpoint.

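### The four secondary endpoints share a second two-sided 0.05 that does not depend on the primary result; a one-sentence gate would close this at no cost in patients or data

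*Protocol*

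**What the plan says.** Section 12.1 says of the primary comparison that "the assessment of this difference will be carried out at an overall two-sided 0.05 level of significance". Section 12.8 splits this into 0.00305 at the interim and 0.049 at the final analysis. Section 12.1, repeated in the Synopsis evaluation plan, then says of the secondaries: "Statistical treatment comparisons on secondary endpoints will also be carried out at an overall two-sided 0.05 level of significance, unless otherwise specified".

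Section 12.6 names the procedure: "In order to control the overall two-sided level of significance at 0.05 across the secondary endpoints, the Benjamini-Hochberg procedure will be used". The family has four members:

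- "Renal Replacement Therapy dependency at day 60" (z-test for proportions)
- "Time-to-Mortality through day 28" (log-rank)
- "Number of ventilator free days (VFD) at day 28" (two-sample t-test)
- time to death through day 60 in patients with severe sepsis (log-rank)

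No section makes these tests conditional on the primary, orders them behind it, or says how they are to be read if it misses. Section 12.9 withholds formal hypothesis tests from the exploratory outcomes only. The 5% control asserted in 12.5 and 12.8 concerns the interim and final tests of the primary endpoint.

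**The concern.** The primary uses the whole of its 0.05. The secondaries then have a 0.05 of their own, available whether or not the primary succeeds. Two of the four are closely tied to the primary: mortality through day 28 is the same outcome cut short, and severe-sepsis mortality is the same outcome in a subset. If the final statistic T* misses 0.049, the rule as written still lets either be declared statistically significant at what the protocol calls an overall 0.05. At stake is how the secondary results may be read when the primary misses. The test of the primary itself is not in question.

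**Working it through.** **Inputs from the protocol.** Primary: overall two-sided 0.05, as 0.00305 at 50% information and 0.049 at the end (12.1, 12.8). Secondaries: Benjamini-Hochberg at 0.05 on four endpoints (12.6). Randomised: 172 per group (12.2). Control 60-day mortality: 50% (12.2).

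**Assumed, because the protocol does not give them.** The correlations between test statistics, the share with severe sepsis, the RRT dependency rate and the distribution of ventilator-free days (VFD).

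**Step 1: the plan's own figure.** Two-sided 0.00305 and 0.049 correspond to |Z| > 2.963 and |Z| > 1.969. With correlation √0.5 = 0.707 between the interim and final statistics, the probability of crossing either boundary under the null is 0.0500. The primary's stated 5% is reproduced.

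**Step 2: both families, independent.** With all nulls true, Benjamini-Hochberg on independent tests rejects something with probability 0.05. The chance of at least one false rejection across both families is therefore 1 − 0.95 × 0.95 = 0.0975.

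**Step 3: both families, correlated.** Five correlated normal statistics were simulated, with the primary tested once at 0.05 and Benjamini-Hochberg at 0.05 on the other four. Assumptions: primary with day-28 mortality 0.80 to 0.95; sepsis share 30% to 70%; VFD with day-28 mortality 0.50 to 0.85; RRT dependency independent. A patient-level simulation with 344 patients and no treatment effect let the correlations arise from the data (primary with day-28 mortality 0.74 to 0.85, with severe sepsis 0.55 to 0.83, with VFD 0.57 to 0.68 in absolute value). RRT dependency was near 0, except 0.84 when deaths stayed in its denominator. Neither simulation models the interim look, the futility option or the sample size re-estimation.

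| Global null | Result |
|---|---|
| Any significant result, correlated normals | 7.1% to 8.5% |
| Any significant result, patient level | 7.1% to 8.5% |
| Any significant result, families independent | 9.75% |
| Any significant result in favour of SCD, patient level | 3.6% to 4.4%, against 2.5% for the primary alone |
| Any secondary significant, primary not | about 2% to 3.5% |
| A mortality secondary significant, primary not, either direction | about 0.6% to 1.6% |

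**Step 4: real effects on the non-mortality secondaries.** Take correlations with the primary of 0.84 (day 28), 0.71 (sepsis), 0.67 (VFD) and 0 (RRT). Make the effects on VFD and RRT dependency real (mean Z of 4) and keep all mortality effects null. Benjamini-Hochberg then relaxes the threshold for the remaining tests:

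| Setting | False rejection within secondaries | False rejection in either family | Mortality secondary significant, primary not |
|---|---|---|---|
| Global null | 4.5% | 7.8% | 1.1% |
| RRT effect real | 6.0% | 8.5% | 2.5% |
| VFD and RRT effects real | 6.4% | 8.6% | 3.7% |
| VFD and RRT effects real, all statistics independent | 7.3% | 11.9% | 6.9% |

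**Step 5: with a gate.** If the secondaries are tested only after a significant primary, the chance of any false rejection is 5.0% in every setting above, because the primary null is true in all of them.

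**The case against.** The strongest reply is that this is silence rather than error. Gating is often left to a statistical analysis plan, the sentence in 12.1 allows for other specification, and a gate could be added with every existing sentence left standing. The protocol promises no trial-wide 5%, states one efficacy hypothesis (12.2), rests its primary objective on 60-day mortality alone, and refers in 12.6 to the secondary nature of these endpoints.

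Much of this stands. No stated error rate is breached, and the protocol nowhere calls the secondaries confirmatory. But it does more than stay silent: it fixes both alpha levels and the procedure, attaches no condition, and uses 12.9 to mark off the outcomes that get no formal test. A gate would narrow what 12.1 and 12.6 now permit.

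Three stronger readings are tempting, and the documents do not support them:

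- **A failed trial could claim its mortality benefit anyway.** Only a day-28 or severe-sepsis result could be called significant, which happens in about 0.6% to 1.6% of global-null trials, roughly half of them favouring SCD. The conclusion on the primary still rests on T* alone.
- **The clinical secondaries are meant to support approval.** The remark "These endpoints are not intended to support a PMA application" follows the sentence on health-economic endpoints. Disclaiming those does not show that the others are intended as support.
- **The two families together spend at most 0.10.** Benjamini-Hochberg controls the false discovery rate, not the familywise error, so that bound is not guaranteed; the last row of step 4 exceeds it.

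**Conclusion.** The point holds as a cheap improvement. The protocol sets two separate two-sided 0.05 families with no gate between them. The error rate it does promise, 5% for the primary over interim and final analyses, is met, and the primary conclusion, power and sample size are untouched.

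Under the global null the cost is a chance of about 7% to 8.5% of some significant result, with 9.75% under independence. The harm that matters most, a mortality secondary called significant after a failed primary, is rare under the global null. It rises to about 2% to 4% if VFD and RRT effects are real and mortality effects are null. These figures rest on assumed correlations and on a single look at the primary, so they should be quoted as ranges.

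**What to change.** Add to 12.1, 12.6 and the Synopsis evaluation plan: secondary endpoints are formally tested only if the primary endpoint is significant (p < 0.00305 at the interim, or T* significant at 0.049 at the final analysis); otherwise they are reported descriptively with 95% confidence intervals. The within-family procedure then applies once the gate is open. The gate does not itself turn Benjamini-Hochberg into familywise control when the primary effect is real.

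The cost is one sentence in three places, with no patients, no data and no change to the primary's power. The downside is that no formal secondary claim can be made when the primary fails.

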## 12.2. DETERMINATION OF SAMPLE SIZE

The efficacy null and alternative hypotheses to be assessed are as follows:

$$H_0: \lambda_{C+S} = \lambda_C$$

vs.

$$H_1: \lambda_{C+S} \neq \lambda_C$$

where  $\lambda_{C+S}$  and  $\lambda_C$  are the true 60 day mortality hazard rates for the CRRT+SCD and CRRT alone groups, respectively. The null hypothesis will be tested at the overall two-sided 0.05 level of significance at 80% power. Under the assumptions:

1.  $\lambda_C = 0.01155$  when time to mortality is measured in days (leading to a 50.0% mortality rate at 60 days for CRRT alone);  $\lambda_{C+S} = 0.00718$  when time to mortality is measured in days (leading to a 35.0% mortality rate at 60 days for CRRT + SCD);
2. As described in the SCD-003 Protocol, CytoPherx has assumed a mortality rate of 50% for control and 35% for SCD.

For the control mortality estimate, a 2004 publication [20] was used which summarized mortality data for subjects with acute renal failure (ARF) requiring renal replacement therapy (RRT) in the intensive care unit. A table from this publication is reproduced below (Table 9). In this table, the mortality of subjects who received CRRT (“Dialysis”) is compared to those who did not (“% Mortality No Dialysis”). A weighted average was calculated by weighting the observed value for “% Mortality Dialysis” by the number of subjects enrolled. We found that the weighted mortality of subjects who received CRRT was 58.3%, based on this literature analysis of 5,810 subjects.

| Variable          | Ref. | Year | N    | Location                    | % Mortality No Dialysis | % Mortality Dialysis |
|-------------------|------|------|------|-----------------------------|-------------------------|----------------------|
| Brivet et al      | [26] | 1996 | 360  | Multicenter, France         | 43%                     | 64%                  |
| Liano et al       | [5]  | 1998 | 748  | Multicenter, Spain          | 53%                     | 79%                  |
| De Mendonca et al | [27] | 2000 | 1411 | 16 countries, Europe        | NA                      | 44%                  |
| Silvester et al   | [28] | 2001 | 299  | Multicenter, Australia      | NA                      | 47%                  |
| Metniz et al      | [7]  | 2002 | 839  | Multicenter, Austria        | 39%                     | 63%                  |
| Clermont et al    | [29] | 2002 | 254  | Pittsburgh, USA             | 23%                     | 57%                  |
| Guerin et al      | [30] | 2002 | 587  | Multicenter, France         | NA                      | 71%                  |
| Metcalfe et al    | [31] | 2002 | 89   | Multicenter, Scotland       | NA                      | 74%                  |
| Mehta et al       | [32] | 2002 | 605  | Multicenter, California USA | 39%                     | 61%                  |
| PICARD            | [20] | 2003 | 618  | Multicenter, USA            | 24%                     | 45%                  |

Table 9 Several recent studies of ARF in the ICU

In our proposed pivotal study, the assumed 60-day mortality rate for subjects receiving CRRT only (control subjects) is 50%. This is a conservative estimate

since, based on the literature, the actual control mortality rate might be expected to be slightly higher.

The observed 60 day mortality rate for SCD therapy was 29.2% in the Pilot study with data available for 24 subjects. For the pivotal study, we have increased the assumed mortality rate to 35% to allow for variability in response across a broader population of subjects and treatment centers;

3. The statistical test to compare treatments is the log-rank test;
4. The study will be carried out using an adaptive design approach; specifically, there will be one formal interim analysis on mortality using the log-rank test after 50% of the subjects achieve 60 day follow-up (or would have achieved 60 day follow-up had they not died or prematurely withdrawn from the study ); treatments will be compared via the log-rank test at this interim analysis using the O'Brien-Fleming two-sided significance levels (0.00305) for the interim analysis (leaving a two-sided significance level of 0.049 for the final analysis); only subjects achieving 60 day follow-up (or who would have achieved 60-day follow-up had they not died or prematurely withdrawn) will be used in the interim analysis; note that if significance is shown in the interim analysis, a decision to stop the trial will only be made after consultation with the FDA; if significance is not shown at this interim analysis, then the DSMB will be provided with sample size re-calculations required to maintain at least 80% power for a statistically significant CRRT+SCD effect by the end of the study, conditioned on the interim results (details are provided below).

Then the required evaluable sample size is 166 subjects per group. To account for attrition, which is expected to be minimal, 172 subjects per group will be randomized. The sample size was calculated using the PASS 2008 software, taking into account the fact the study may be stopped for overwhelming efficacy at the interim analysis using the log-rank test at the O'Brien-Fleming significance level of 0.00305.

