## **12.8. INTERIM ANALYSIS/ADAPTIVE DESIGN**

There will be one formal interim efficacy analysis on the primary endpoint of time to all-cause mortality by 60 days, to be inspected by the DSMB. This analysis will be performed on the ITT analysis set after 50% of the planned number of patients achieved 60 day follow-up (or would have achieved 60 day follow-up at the time if the patient did not die or prematurely withdraw). Using the Lan-DeMets function with the O'Brien-Fleming philosophy, the two-sided treatment comparison significance levels to be used at the interim and final analysis are 0.00305 and 0.049, respectively. If the DSMB recommends stopping the study at the interim analysis (i.e., if the two-sided p-value for the primary endpoint is below 0.00305 at the interim analysis), a decision to stop the study will only be made after consultation with the FDA.

If the DSMB does not recommend stopping the study at the interim analysis for overwhelming efficacy, the DSMB may recommend stopping the study for futility if the interim estimate of survival for the CRRT alone group is larger than that for the CRRT + SCD group (in which case, no further enrollment of patients will be carried out, but patients already enrolled at the time of the decision to stop for futility will continue to be followed for 60 days. Otherwise, the DSMB will be presented with a proposed increase in sample size for achieving a statistically significant treatment difference on the primary endpoint by the time of the final analysis. The sample size re-estimation will be performed based on the approach suggested by Cui, Hung and Wang (1999) using the ratio of the initial estimate of effect size,  $E_0$ , which is the difference between Kaplan-Meier estimates of 60 day mortality rate (CRRT + SCD minus CRRT alone) for the initial sample size determination used for study design, and the observed effect size,  $E$ , which is the treatment difference in estimated Kaplan-Meier estimate of the 60 day mortality rate at the time of the interim analysis.

The number of patients initially estimated,  $N_o$  (=172), is readjusted to determine the new total number of required patients,  $N$ , using the following formula:

$$N = \left\lceil \frac{E_o}{E} \right\rceil^2 N_o$$

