This method will provide the required number of patients for the second stage of the study. In case the sample size re-assessment results in an increase of the number of subjects, the DSMB may recommend changing the study accordingly (if however the increase in sample size is more than twice the number of originally planned subjects, the DSMB may recommend continuing the study until twice the number of originally planned patients are randomized). In case the sample size re-assessment results in an adaption to less than the original planned sample size, the study will be continued as originally planned (until 172 subjects are randomized).

The statistical methodology used to compare treatments at the interim and final analysis is discussed above. The overall type I error of 5% is controlled as has been confirmed by simulations.

The DSMB will periodically review safety data. A DSMB charter will be written outlining the safety data to be inspected periodically by the DSMB. The DSMB may recommend stopping the study for safety issues, and this recommendation does not need to necessarily be based on statistical significance.

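### The re-estimation rule, capped at twice the planned number, keeps 80% conditional power only when the interim mortality difference is about 10 points or more, and the protocol does not say so

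*Protocol*

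**What the plan says.** Section 12.2 sets the design: "The null hypothesis will be tested at the overall two-sided 0.05 level of significance at 80% power", on the assumption that "CytoPherx has assumed a mortality rate of 50% for control and 35% for SCD". Its item 4 describes one interim analysis at half the planned patients and promises the DSMB, if that analysis is not significant, "sample size re-calculations required to maintain at least 80% power for a statistically significant CRRT+SCD effect by the end of the study". It adds that this power is conditional on what the interim shows and that details follow later.

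The details are in Section 12.8. The new size is found by "using the ratio of the initial estimate of effect size" to the observed one, squared, times the planned number: N = (E0/E)² × N0. If this gives less than the planned number, the trial continues as planned. If the increase is too large, "the DSMB may recommend continuing the study until twice the number of originally planned patients are randomized". Section 12.5 fixes the final test as T* = √0.5·Z(1) + √0.5·Z(2), whatever the new size.

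**The concern.** The formula rescales the fixed-sample design from the planned difference to the observed one. It has no term for the first-stage statistic already in hand, for the final boundary, or for the fixed half-and-half weights of T*, all of which determine conditional power. The cap then limits N without any statement that the promised power lapses when it binds. Neither section says over which interim results 80% is reached.

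This matters because the DSMB has to decide whether to recommend enlarging a trial in critically ill patients, and Section 12.2 describes the numbers it will see as preserving 80% power. For weak interim results the actual figure is far lower. Such results are not rare. With true rates of 50% and 35%, the standard error of the interim difference is √(0.25/86 + 0.2275/86) = 0.0745. A difference between 0 and 10 points then has probability Φ(−0.67) − Φ(−2.01), about 23%.

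**Working it through.** **Inputs from the protocol.** "The statistical test to compare treatments is the log-rank test" (12.2). The final level is 0.049 two-sided (12.2 and 12.8), so the critical value is c = 1.969. Planned mortality is 50% and 35%, so E0 = 15 points (12.2). N0 = 172 per group (12.2), with the interim at half of that, 86 per group. T* has weights 0.5 and 0.5 (12.5). Floor and cap are as in 12.8.

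**Assumptions.** Control mortality is 50% at the interim (45% and 60% as sensitivity). The observed difference E continues after the interim. The cap means 344 per group in total.

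**The plan's own figure.** The hazard ratio is 0.00718/0.01155 = 0.622, with log −0.475. Events needed: 4 × (1.969 + 0.842)² / 0.475² ≈ 140. Dividing by the mean mortality 0.425 and by 2 gives 165 per group, against 166 stated. The design size is reproduced.

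**Conditional power.** T* exceeds c when Z(2) > c√2 − z1 = 2.784 − z1, so

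CP = Φ(θ2 − 2.784 + z1), with θ2 = z1 × √((N − 86)/86).

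For the log-rank test, z1 = −ln(HR) × √(events)/2 with HR = ln(1 − 0.50 + E)/ln(0.50).

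- *E = 10 points.* HR = 0.737, −ln HR = 0.305, interim events 172 × 0.45 = 77.4, z1 = 1.343. The formula asks for (15/10)² × 172 = 387, capped at 344. θ2 = 1.343 × √3 = 2.325. CP = Φ(2.325 − 1.441) = 81%. A pooled two-proportion Z gives z1 = 1.318 and CP = 79%.
- *E = 5 points.* z1 = 0.669, N capped at 344, θ2 = 1.158. CP = Φ(1.158 − 2.115) = 17%. Uncapped, N = 1,548, θ2 = 2.756 and CP = 74%.

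The same steps give, as log-rank / two-proportion Z:

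| Interim difference (points) | Formula N per group | CP, capped at 344 | CP, uncapped |
|---|---|---|---|
| 12 | 269 | 88% / 87% | 88% / 87% |
| 10 | 387 | 81% / 79% | 86% / 84% |
| 9 | 478 | 70% / 68% | 84% / 82% |
| 8 | 605 | 56% / 54% | 82% / 80% |
| 7 | 790 | 41% / 39% | 80% / 78% |
| 5 | 1,548 | 17% / 16% | 74% / 72% |
| 2 | 9,675 | 2% / 2% | 62% / 60% |

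**Where 80% is lost under the cap.** At 344 per group CP = Φ(2.732·z1 − 2.784), so 80% needs z1 ≥ (2.784 + 0.842)/2.732 = 1.327. That is E = 9.9 points by log-rank and 10.1 by proportions, and about 9.8 to 10.2 across the control rates tried. The cap itself starts to bind at 15/√2 = 10.6 points.

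**Where 80% is lost without the cap.** At 50% control mortality the crossing is 7.1 points (log-rank) or 7.9 (proportions). The lowest across the variants is 6.3. With a weak interim result, half the weight of T* stays on a Z(1) near zero, and the formula does not compensate.

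**Ordinary power at the observed effect, under the cap.** At 10 points the log-rank drift for 344 per group is 0.305 × √309.6/2 = 2.685, so power is Φ(2.685 − 1.969) = 76% (75% by proportions). At 5 points it is 26%.

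**Literal reading of the cap.** Section 12.8 applies the cap when the *increase* exceeds twice the planned number, that is when N > 3 × N0, or E < 15/√3 = 8.7 points. CP is then about 83–86% (log-rank) from 8.7 to 10 points. It drops to about 65% just below 8.7, where the size falls back to 344 per group, and follows the capped column from there.

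**The case against.** The best defence is that Section 12.2 never uses the term conditional power. The phrase could mean 80% power at the interim effect estimate, which the uncapped formula supplies almost by construction, and the cap is stated openly in the section to which 12.2 refers. This stands in part: the wording is open to that reading, and the uncapped formula meets it. It does not rescue the claim, because ordinary power at the observed effect is also only 75–76% at 10 points and 26% at 5 once the cap binds, and no section says so.

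The figures also depend on the observed trend continuing. If the design difference of 15 points held after the interim, conditional power would stay above about 85% for the interim differences checked (3 points and up). But the rule itself uses the observed E, so the current trend is its own premise.

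A reader might go further than the document allows in four ways.

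- One might infer that the formula fails everywhere below 10 points. That threshold belongs to the cap; the formula alone holds down to about 7 to 8 points.
- One might call the 87–88% at 12 points an error. The promise is for at least 80%, so the excess is consistent with it.
- One might say that any small positive difference commits 344 further patients. Section 12.8 says only that the DSMB may recommend an increase, and Section 11 lets it recommend stopping for safety or futility.
- One might suspect inflated type I error. Nothing here bears on it, because T* keeps its pre-specified weights.

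**Conclusion.** The point holds as a wrong stated property of the design. The rule in Section 12.8 does not maintain at least 80% power given the interim results, as Section 12.2 says it will. Under the cap, 80% conditional power is reached only at an interim difference of about 10 points or more. Below that it falls quickly, to 54–56% at 8 points and 16–17% at 5.

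This rests on 50% control mortality (little changed at 45% or 60%), a continuing trend, 172 taken as the number per group, and the cap taken as a total of 344 per group. On the literal reading of the cap the shortfall starts at about 8.7 points instead. Sections 12.5 and 12.8 in places call 172 the total; taken that way, conditional power at 10 points would be about 42%. The planned size and the validity of the final test are not in question.

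**What to change.** Three wording changes are enough.

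1. In Section 12.2, item 4, say that 80% conditional power is reached only when the interim difference is about 10 points or more, and is lower below that because of the cap.
2. In Section 12.8, say that the DSMB receives, alongside N, the conditional power under T* at the proposed (capped) size.
3. In Section 12.8, make clear that the cap is on the total number randomized, not on the increase.

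The cost is a short protocol wording change and a less favourable stated power. The test, its weights and its significance levels stay as they are.

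Solving the second-stage size for 80% conditional power under T*, setting a floor below which no increase is proposed, and announcing N in fixed steps are optional design choices. The error does not require them. Replacing the formula would mean amending the pre-specified rule and repeating the simulations.
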